### Statistical analysis

Data will be checked for normal distribution. Three different types of analysis will be performed.

#### Intervention group Vs control group

To examine the efficacy of the intervention, the outcome measures of the intervention group and control group will be compared at each of time points T0 and T1 using mixed linear regression analysis with group (intervention/control) as independent variable and the outcome measures (see Table2) as separate dependent variables.

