## Methods/design

### Study design

The current study is a multi-center (4 sites) randomized controlled trial, with the control group also entering the training arm directly following completion of the initial protocol. After randomization (1:1), subjects in both groups will perform a test battery of exercise tests, questionnaires, and other measurements (see study outcomes) (T0 measurement). Thereafter, subjects in the intervention group will receive an exercise training regimen, while the subjects in the control group will continue to receive standard care over a 12-week period. Subsequently, subjects in both groups will repeat the battery of tests from T0 (T1 measurement). Subjects in the intervention group will then receive individual advice based on their T1 results and educated on the physical activity guidelines for children [20] in order to help maintain fitness levels following the intervention. Subjects in the control group will enroll in the exercise training program. Following this 12-week period, subjects in both groups will repeat the battery of tests from T0 and T1 (T2 measurement) and the subjects in the control group will receive individual feedback in the same manner as the intervention group at T1. After 12 weeks, the subjects in the control group will repeat the battery of tests from T0, T1, and T2 (T3 measurement). See Figure1 for a flow diagram of the study design.

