### Power calculation

A power calculation was performed based on previously published data relating to one of the primary outcome measures: VO_2peak/kg_. The mean ± standard deviation VO_2peak/kg_ of patients with JDM (in remission) is 33 ± 8 ml·kg^-1^·min^-1^[13]. The aim of this training intervention is to improve VO_2peak/kg_ by at least 22%, which is the weighted mean improvement in exercise training studies in adults with inflammatory myositis [17]. Given an 80% probability of detecting a treatment effect, with significance set at 0.05 (two-tailed), the required number of total subjects is 22; 11 in each of the 2 groups. Upon factoring in a 20% (*n* = 5) chance of missing observations and/or drop-outs, the total sample size increase to 27 patients. For simplicity in the randomization process, we want to include 30 patients.

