#### Intervention in control group

To examine the efficacy of the intervention in the control group, changes in outcome measures between T0 and T1 (usual care) will be compared with the changes in outcome measures between T1 and T2 (intervention) using a paired samples *T*-test.

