#### “Wash-out” effect in intervention and control group

Repeated measures ANOVA analyzes will be performed to examine whether the effects of the intervention are maintained after 12 weeks. Specifically, the outcome measures of both groups will be compared between post-12-week usual care after intervention vs. post-intervention and post-12-week usual care after intervention vs. pre-intervention.

Results will be presented as linear regression coefficients representing mean group differences with their corresponding 95% confidence intervals (CI). Statistical significance will be defined as cases in which the 95% CI does not include the null value. Nominal variables will be analyzed using chi-square analysis. All results will be analyzed using the modified intention to treat approach which means that all subjects will be included in the groups to which they are randomized, and the researchers make efforts to obtain outcome data for all subjects, even if they do not complete the full intervention [50].

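### The randomised T1 comparison is not adjusted for the T0 value of the outcome, so it is unbiased but gives up precision that the trial has already collected

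*Protocol article*

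**What the plan says.** In the Protocol article, section Intervention group Vs control group, the outcomes of the two arms "will be compared at each of time points T0 and T1 using mixed linear regression analysis with group (intervention/control) as independent variable", with each Table 2 outcome analysed separately. No T0 covariate, time term, group-by-time term or change score is named. The end of the Wash-out section fixes the form of the result: "Results will be presented as linear regression coefficients representing mean group differences with their corresponding 95% confidence intervals (CI").

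The T0 measurement exists in both arms. Study design has the full battery done at T0, and then: "Subsequently, subjects in both groups will repeat the battery of tests from T0 (T1 measurement").

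Pre-intervention values are used in two other analyses. For the controls alone, "changes in outcome measures between T0 and T1 (usual care) will be compared with the changes in outcome measures between T1 and T2 (intervention") by a paired t-test. The wash-out analysis includes the contrast "post-12-week usual care after intervention vs. pre-intervention". Neither of these is the randomised comparison.

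**The concern.** The article fixes both the predictor and the time points of the main efficacy analysis, and the version it fixes leaves out the covariate likely to be the most useful one. Children aged 8 to 18 can be expected to differ widely in oxygen uptake and muscle force before any training. An unadjusted T1 comparison leaves all of that between-child variation in the error term.

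At stake is the chance of detecting a real training effect in a trial of 30 children with a rare disease, where more patients are hard to find. The same model is applied to every outcome in Table 2. The T0 comparison adds nothing on efficacy, because a group difference before training is due to chance when allocation is random.

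**Working it through.** **Inputs from Power calculation.** Peak oxygen uptake per kg "of patients with JDM (in remission) is 33 ± 8" ml/kg/min. The aim is to raise it "by at least 22%, which is the weighted mean improvement in exercise training studies in adults with inflammatory myositis". The error rates: "Given an 80% probability of detecting a treatment effect, with significance set at 0.05 (two-tailed"). The stated need is 11 per group, 22 in total; the planned number is 30, with a 20% allowance for loss.

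- Difference: 0.22 × 33 = 7.26 ml/kg/min, or 7.26/8 = 0.91 SD.
- Full recruitment without loss: 30/2 = 15 per arm.
- After the 20% allowance: 30 × 0.8 = 24, or 12 per arm.

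**The plan's own figure.** For an unadjusted two-group comparison, n per group = 2(1.96 + 0.84)² × 8²/7.26², which is just over 19 and rounds up to 20; the t distribution gives 21. The stated 11 is not reproduced. With 11 per group, unadjusted power is 53% (t). A residual SD of about 5.8 to 6.1 would give 11, which under T0 adjustment means r of about 0.65 to 0.69, but no such assumption is stated. The sample-size mismatch is a separate matter. It is shown here only because the unadjusted analysis does not reach the stated 80% even at 15 per arm.

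**Unadjusted T1 comparison.** The standard error is 8√(2/n): 2.92 at n = 15 and 3.27 at n = 12. The noncentrality is 7.26/2.92 = 2.49 and 7.26/3.27 = 2.22. With 2n − 2 degrees of freedom, power is 67% and 57%.

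**T0-adjusted comparison.** The residual SD is 8√(1 − r²), with 2n − 3 degrees of freedom. The article does not give r, so a range is assumed.

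| r (assumed) | Variance removed (r²) | Residual SD | Power, 15 per arm | Power, 12 per arm | 95% CI half-width, 15 per arm |
|---|---|---|---|---|---|
| unadjusted | – | 8.00 | 67% | 57% | 6.0 |
| 0.3 | 9% | 7.63 | 71% | 60% | 5.7 |
| 0.5 | 25% | 6.93 | 79% | 69% | 5.2 |
| 0.6 | 36% | 6.40 | 85% | 76% | 4.8 |
| 0.7 | 49% | 5.71 | 92% | 84% | 4.3 |
| 0.8 | 64% | 4.80 | 98% | 94% | 3.6 |

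The adjusted figures allow for the lost degree of freedom but not for the small extra variance from chance T0 imbalance, so they are slightly optimistic.

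**Does the word mixed change this?** Suppose T0 and T1 are fitted jointly with a free group difference at each time. With complete data, the T1 difference is then the same as from the T1 data alone. The T0 data improve the T1 estimate only if the T0 means are constrained equal or T0 enters as a covariate.

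**Would a change score do instead?** Its variance is 2(1 − r) times the unadjusted variance, so it helps only if r exceeds 0.5. At r = 0.3 it needs 28 per group against 21 unadjusted; adjustment needs 19.

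**The case against.** The strongest defence is that randomisation already makes the unadjusted T1 comparison unbiased with correct type I error. This stands: the fault is lost efficiency of unknown size, not a wrong estimate. Stratification by age and gender in small blocks also limits imbalance on two obvious drivers of oxygen uptake and force. That stands too, but it does not remove the remaining variation between children, and neither factor is named in the model.

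A second defence is that a condensed article leaves model detail to a fuller document, and that mixed regression on two time points hints at time and group-by-time terms. Even if so, an unconstrained model of that kind yields the same T1 estimate with complete data. The article also goes beyond silence: it names the predictor and the comparison.

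Four stronger readings are tempting, but the article does not support them:

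- **T0 is ignored altogether.** It is compared as an outcome in its own right, and it is used within subject in the control-group and wash-out analyses. It is unused only as an adjustment of the randomised comparison.
- **Most of the precision is lost.** In variance terms that requires r above about 0.71, and the article gives no r. At 0.3 the loss is small.
- **The coefficient is half the true effect.** That would follow from one group coefficient pooled over T0 and T1, but the text compares the groups at each time point, which excludes pooling.
- **A chance T0 imbalance carries over in full.** With equal SDs, the expected carry-over is r times the imbalance.

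**Conclusion.** The point holds as one of efficiency, and it should be fixed. As written, the randomised T1 comparison is unbiased but does not use the T0 value of the same outcome, and the T0 between-group test is uninformative under randomisation. On the article's own SD and target difference, the unadjusted analysis has 67% power with all 30 children and 57% after the planned allowance for loss. With adjustment and r between 0.5 and 0.8, these become 79% to 98% and 69% to 94%; at r = 0.3 the gain is only about 3 to 4 percentage points.

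The size rests on assumptions: the r values, the cross-sectional SD of 8 applying at T1 in both arms, and a true difference of 7.26. The figures concern peak oxygen uptake per kg only; r may differ for the other outcomes. T0 is measured after randomisation but before training, so adjustment also assumes that knowing the allocation did not alter performance at T0. The article gives no sign that it did, and the assessors are to be blinded.

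**What to change.** State the efficacy analysis in one of two equivalent forms:

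- a regression of the T1 outcome on group and the T0 value of the same outcome (ANCOVA); or
- a mixed model of T0 and T1 with time and group-by-time terms, in which the T0 mean is constrained equal between arms.

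Name the T1 group difference from that model, with its 95% confidence interval, as the efficacy estimate. Drop the between-group test at T0 and show T0 values descriptively. If power is restated for the adjusted analysis, give the assumed T0-T1 correlation.

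The cost is one sentence of analysis text and one degree of freedom. No new data are needed, because the T0 battery is already planned in both arms.

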**Methods/design:**

Subjects (*n* = 30) will include 8–18 year olds diagnosed with JDM. The intervention consists of an individually tailored 12-weeks home-based exercise training program in which interval training on a treadmill is alternated with strength training during each session. The program is based on previous literature and designed with a defined frequency, intensity, time, and type of exercise (FITT principles). Primary outcome measures include aerobic exercise capacity, isometric muscle strength, and perception of fatigue. The study methodology has been conceived according to the standards of the CONSORT guidelines. The current study will be a multi-center (4 Dutch University Medical Centers) RCT, with the control group also entering the training arm directly after completion of the initial protocol. Randomization is stratified according to age and gender.

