### Subjects

All patients diagnosed with JDM by a pediatric rheumatologist/immunologist according to the Bohan and Peter criteria between the ages of 8 and 18 years from 4 outpatient clinics in the Netherlands will be assessed for eligibility. The 4 outpatient clinics include the Wilhelmina Children’s Hospital University Medical Center (UMC) in Utrecht, the Beatrix Children’s Hospital UMC in Groningen, the Sophia Children’s Hospital Erasmus Medical Center in Rotterdam, and the St. Radboud Children’s Hospital UMC in Nijmegen.

Patients will be excluded for eligibility upon (1) a medical status that contraindicates any form of exercise testing; (2) an insufficient understanding of the Dutch language in the patient and/or the parents/caregivers; (3) the presence of medical events that might intervene with the outcome of testing and/or the trial (such as a planned operation) and/or (4) a negative advise from the rheumatologist and/or physiotherapist based on resent relapse or no limitations in exercise tolerance (in other words: the patient was either not good enough or too good). All eligible patients will be asked to participate in the study. All parents/caregivers as well as subjects >12 years of age years must provide informed consent before enrolment in this study, which is approved by the Medical Ethics Committee of the UMC Utrecht, the Netherlands.

The flow of the subjects in the study will be depicted in the CONSORT Flowchart format [21]. The reasons for non-eligibility, declination to participate, and non-completion of the study will be reported in this flowchart as well.

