### Randomization and blinding

Included subjects will be stratified according to age (≤ or >12 years) and gender after which they will be randomized to either the intervention or the control group. The randomization process will be performed by a person with no clinical involvement in the trial. Blocking is used to ensure close balance of the numbers in each group at any time during the trial. Randomly varying the block size (2 or 4) reserves the unpredictability of the sequence. The sequences will be concealed until interventions are assigned. The researchers performing the assessments, as well as those charged with data analyzes will be blinded to treatment allocation.

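### Randomisation is stratified by age and gender but the between-group model names only group; read literally, it is conservative for outcomes that depend on age or gender

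*Protocol article*

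**What the plan says.** Design. Under Randomization and blinding, "Included subjects will be stratified according to age (≤ or >12 years) and gender after which they will be randomized". Within strata, "Blocking is used to ensure close balance of the numbers in each group at any time during the trial", with block sizes of 2 or 4 varied at random. The abstract repeats the stratification: "Randomization is stratified according to age and gender".

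Analysis. Under Intervention group Vs control group, the outcomes "will be compared at each of time points T0 and T1 using mixed linear regression analysis". The same sentence then lists the terms of that model: "with group (intervention/control) as independent variable and the outcome measures (see Table2) as separate dependent variables". No section places age, gender or a T0 value in this model. Age and gender appear again only as descriptors under Baseline description of groups.

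Decision rule. At the end of the statistical section, "Statistical significance will be defined as cases in which the 95% CI does not include the null value". The accuracy of the interval therefore decides each result.

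Population and outcomes. Patients are "between the ages of 8 and 18 years". Among the primary outcomes, Table 2 lists several that are not scaled to body size: VO2peak in l/min, O2 pulse, and knee and hip force in newtons.

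**The concern.** Stratified blocks make the two arms more alike on age and gender than simple randomisation would. That lowers the true sampling variance of the group difference for any outcome these factors predict. A model containing only group still counts their contribution as residual noise, so its standard error is larger than the real variability of the estimate. The interval then covers more than 95% of the time and the test rejects less than 5% of the time under the null.

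At stake are accurate intervals and some precision, in a trial of 30 children spanning ten years of growth. The article does not simply leave the model to a later document: it names the method, the independent variable and the dependent variables, and these do not match the stated randomisation.

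**Working it through.** **Inputs from the protocol article.** N = 30, 1:1; four strata (age cut at 12, by gender); blocks of 2 or 4; two-sided 0.05; mean 33 and SD 8 ml/kg/min; target improvement 22%.

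**Effect size and starting power.** 0.22 × 33 = 7.26; 7.26 / 8 = 0.9075 SD. With 15 per group, a two-sample t-test has 67% power (normal approximation 70%). The same inputs give about 20 per group for 80% power, so the article's 11 per group is not reproduced. That is a separate matter and nothing below depends on it.

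**Assumptions, because the documents give no figures.** Age uniform on 8 to 18; both genders equally likely; age and gender together explain a share R² of outcome variance (85% of that share from age, linear; 15% from gender); residual T0-T1 correlation 0.7. There were 6,000 simulated trials per null setting and 3,000 per effect setting. The Monte Carlo standard error at 5% is √(0.05 × 0.95 / 6000) = 0.3 percentage points.

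**Mechanism.** With equal arms the group-only standard error is about σ√(4/N) = σ√(4/30) = 0.365σ, whatever R² is. The true SD of the estimate falls with the balance achieved. At R² = 0.5 the mean interval width is 1.494 SD, so the reported SE is 1.494 / (2 × 2.048) = 0.365, while the simulated SD of the estimate is 0.297. The effective critical value is 2.048 × 0.365 / 0.297 = 2.52, and P(|t28| > 2.52) is about 1.8%. The simulated rejection rate is 1.9%.

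**T1 comparison without T0 (CI width in SD units).**

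| R² | Type I error, group only | Type I error, + age, gender | CI width, group only | CI width, + age, gender | Power at 0.9075 SD, group only | Power, + age, gender |
|---|---|---|---|---|---|---|
| 0 | 5.3% | 5.5% | 1.48 | 1.50 | 67% | 66% |
| 0.1 | 4.1% | 5.2% | 1.49 | 1.43 | 68% | 71% |
| 0.3 | 2.7% | 5.4% | 1.49 | 1.26 | 69% | 81% |
| 0.5 | 1.9% | 5.1% | 1.49 | 1.07 | 70% | 92% |
| 0.7 | 0.6% | 4.8% | 1.50 | 0.82 | 70% | 99% |

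Runs in which age alone carries R² agree. Across all runs, group-only type I error is 2.4 to 3.1%, 1.7 to 2.0% and 0.6 to 0.9% at R² = 0.3, 0.5 and 0.7.

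**T1 comparison with the T0 value in the model.**

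| R² | Type I error, T0 only | CI width, T0 only | CI width, T0 + age, gender |
|---|---|---|---|
| 0 | 5.3% | 1.079 | 1.093 |
| 0.1 | 4.9% | 1.033 | 1.039 |
| 0.3 | 4.5% | 0.924 | 0.916 |
| 0.5 | 4.4% | 0.791 | 0.774 |
| 0.7 | 4.8% | 0.622 | 0.600 |

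The largest gain here is 1 − 0.600/0.622 = 3.5%; with age alone carrying R² = 0.7, half-widths of 0.311 and 0.299 give 3.9%. At R² = 0.3, power is 97% with or without age and gender.

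**Linear age and the 12-year cut.** For age uniform on 8 to 18, the two age groups have means 10 and 15 and shares 0.4 and 0.6. Variance between them is 0.4 × 0.6 × 5² = 6, against a total of 10²/12 = 8.33, so the cut carries 72% of the variance of age. Neither term contains the other. With the cut and gender instead of continuous age, type I error is 5.0, 4.9 and 4.7% at R² = 0.3, 0.5 and 0.7, and CI widths are 1.32, 1.18 and 1.02.

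**The case against.** The best reply is that the sentence is condensed. A mixed model over T0 and T1 must carry more terms than the one it lists, the article does not say that the comparison is unadjusted, and covariate lists are often left to an analysis plan. If the model estimates the difference in change, or includes T0, most of the age effect cancels; simulated type I error is then 4.4 to 5.3%. This stands as a limit on size. It does not remove the point, because the article states the comparison at each time point and names neither a baseline term nor a time-by-group term.

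Three stronger readings are tempting and are not supported:

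- A reader might charge the full difference in interval width to the missing stratification factors. Without T0, the group-only interval is 1.491/1.258, 1.494/1.065 and 1.503/0.822 times the adjusted one, that is 19, 40 and 83% wider at R² = 0.3, 0.5 and 0.7. Once T0 is in the model, at most about 4% remains, so most of this reflects the absent baseline value.
- A reader might infer that power collapses, to 30% at R² = 0.7. That follows only if the effect is fixed at 1.1 residual SD, a value not in the documents. It then shrinks to 1.1 × √0.3 = 0.60 total SD. At the protocol's 0.9075 SD, group-only power does not fall; what is forgone is a possible gain.
- A reader might infer that every interval misses its coverage, or that the powered outcome is hit hardest. With no dependence on age or gender there is no effect, and VO2peak/kg is already divided by body mass. The documents do not show how strongly it depends on age.

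**Conclusion.** The mismatch between randomisation and model is real and should be corrected, but it does not threaten validity. It holds for outcomes that depend on age or gender, under a literal reading of the model with no T0 term. There the stated 95% interval is too wide and the test conservative, with type I error from about 4% at R² = 0.1 to below 1% at R² = 0.7. The R² values and the T0-T1 correlation of 0.7 are assumptions. For outcomes unrelated to age or gender nothing is lost, and with T0 in the model the remaining benefit of age and gender is a few per cent of interval width. The error runs towards missed effects, not false positives.

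**What to change.** In the section Intervention group Vs control group, state that the T1 comparison includes gender, age and the T0 value of the outcome as fixed effects alongside group. Age may be continuous, which captures more variance if the relation is roughly linear. A linear term does not contain the 12-year cut, so use the indicator for 12 or under versus over 12 if the exact stratification factor is wanted.

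The cost is one clause, on data already collected. Age and gender use two degrees of freedom and T0 one more. For an outcome unrelated to age or gender, adding those two widens the interval by about 1% (1.484 to 1.500 SD without T0; 1.079 to 1.093 with it).

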### Type - strength training

The aim of the strength training program is to improve the muscle strength of proximal muscle groups, since these tend to be most affected in JDM. Along with the recommendation that strength training in youth should include large muscle groups [3], the following 3 exercises are included: squat, abdominal crunch, and push-up. To prevent muscle damage, the exercises are concentric in nature and against gravity (no additional weight lifting). A ball is implemented in some of the exercises to maintain the playfulness of the exercise.

Interval training on the treadmill and strength training will be performed in an alternating fashion during each session.

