### Study outcomes

#### Efficacy

The primary and secondary efficacy outcome measures along with the tools for these assessments are described below and in Table2.

**Table 2 T2:** The primary and secondary study outcomes and the accompanying measurement tools used

	**Items**	**Range**	**+/−**
**Aerobic exercise capacity***(Maximal exercise test on treadmill)*			
VO_2peak_ [l·min^-1^]	na	>0	+
VO_2peak/kg_ [ml·kg^-1^·min^-1^] ^1^	na	>0	+
O_2_ pulse [ml·beat^-1^]	na	>0	+
Endurance time [min]	na	>0	+
VO_2VAT_ [l·min^-1^]	na	>0	+
VO_2VAT/kg_ [ml·kg^-1^·min^-1^]	na	>0	+
**Isometric muscle strength***(Hand-held dynamometry – Break method)*			
Maximal force right knee extensors [N]	na	>0	+
Maximal force left knee extensors [N]	na	>0	+
Maximal force right hip flexors [N]	na	>0	+
Maximal force left hip flexors [N]	na	>0	+
**Perception of fatigue***(PedsQL Multidimensional Fatigue Scale – patient form)*			
Total score	18	0-100	+
Subscale *General Fatigue* score	6	0-100	+
Subscale *Sleep/Rest Fatigue* score	6	0-100	+
Subscale *Cognitive Fatigue* score	6	0-100	+
**Muscle soreness***(10-cm Visual Analogue Scale muscle soreness)*			
Visual Analogue Scale muscle soreness [cm]	na	0-10	-
**Muscle function***(BOT-2 Subscale 8 – Strength)*			
Total score	5	0-42	+
Item *Distance standing long jump* [m]	na	>0	+
Item *Amount of sit-ups in 30 s*	na	≥0	+
Item *Amount of push-ups in 30 s*	na	≥0	+
Item *Time wall sit* [s]	na	0-60	+
Item *Time V-up* [s]	na	0-60	+
**Muscle function***(Childhood Myositis Assessment Scale)*			
Total score	14	0-52	+
**Functional sub maximal aerobic exercise capacity***(6-Minute Walk Test)*			
Distance [m]	na	>0	+
**Physical activity enjoyment***(Physical Activity Enjoyment Scale)*			
Total score	17	17-119	+
**Quality of life***(PedsQL Generic Core Scale – patient form)*			
Total score	23	0-100	+
Subscale *Physical Functioning* score	8	0-100	+
Subscale *Emotional Functioning* score	5	0-100	+
Subscale *Social Functional* score	5	0-100	+
Subscale *School Functioning* score	5	0-100	+
**Functional ability***(Childhood Health Assessment Questionnaire 30 + 8)*			
Subscale *Dressing* score	4	0-3	-
Subscale *Arising* score	2	0-3	-
Subscale *Eating* score	3	0-3	-
Subscale *Walking* score	2	0-3	-
Subscale *Hygiene* score	5	0-3	-
Subscale *Reach* score	4	0-3	-
Subscale *Grip* score	5	0-3	-
Subscale *Activities* score	5	0-3	-
Subscale *School/Extracurricular* score	8	0-3	-
Disability score [%]	38	0-100	-
Visual Analogue Scale pain [cm]	na	0-10	-

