*Isometric muscle strength* of the proximal muscle groups in the lower extremities will be measured on both the right and left sides with a calibrated CITEC hand-held dynamometer (C.I.T. Technics, Groningen, the Netherlands). Both the extensors of the knee joint and the flexors of the hip joint will be assessed with 3 consecutive measurements according to the ‘break method’, wherein the examiner gradually overcomes the muscle force and stops at the moment the extremity gives way [34]. The highest value of the 3 repetitions will be recorded. All within-subject tests will be performed by the same assessor using the same hand-held dynamometer to prevent inter-observer and inter-instrument bias [34].

*Perception of fatigue* will be measured with the Dutch translated PedsQL Multidimensional Fatigue Scale. This scale, designed to measure fatigue in pediatric patients, reflects 3 subscales: general fatigue, sleep/rest fatigue, and cognitive fatigue [35-37].

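### Primary leg strength is tested as four separate single-limb outcomes with no summary per muscle group, although the plan asks no question about sides

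*Protocol article*

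**What the plan says.** The abstract (Methods/design) states: "Primary outcome measures include aerobic exercise capacity, isometric muscle strength, and perception of fatigue". Under Primary study outcomes, strength "will be measured on both the right and left sides", for knee extensors and hip flexors, and the best of three attempts is recorded for each limb. Table 2 carries the resulting four maximal forces as four rows, with no mean or sum of the sides.

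The section Intervention group Vs control group fits a mixed linear regression with group as the independent variable and "the outcome measures (see Table2) as separate dependent variables". The closing paragraph of the Statistical analysis section calls a result significant when its own 95% confidence interval excludes the null.

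Under Type - strength training, the aim is stated for proximal muscle groups without naming a side, and "the following 3 exercises are included: squat, abdominal crunch, and push-up". The other component is treadmill walking or running. No hypothesis about one leg, a dominant limb or asymmetric disease appears in the article.

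**The concern.** Right and left readings of the same muscle group in the same child are two noisy measurements of what the trial treats as one thing. Testing them apart has two consequences.

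- The two sides can fall on different sides of the significance line by chance when the true effect is identical. Fatigue has a total score, and within aerobic capacity VO2peak/kg is marked as the variable behind the power calculation. Strength has neither a summary nor a lead variable, so a result significant on the right only has no planned reading.
- Each single-limb estimate keeps all of its own reading error, part of which would average out across sides. With 30 children planned, precision that costs nothing is worth having.

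**Working it through.** **Inputs.** From the document: four limb rows (Table 2), separate models, a two-sided 5% criterion per outcome, and 30 children randomised 1:1, so 15 per arm. The document gives no sample-size figure, SD or left-right correlation for strength, so there is no planned figure to reproduce. The correlation r and the power per limb are assumptions, shown over a range. Here r is the correlation between sides, across children, of whatever quantity is compared between groups (T1 values, or T1 values adjusted for T0). Equal variance on both sides is assumed.

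**Precision.** Var(mean of sides) / Var(one side) = (1 + r)/2. The confidence-interval width ratio is its square root. For example, r = 0.7 gives (1.7)/2 = 0.85, square root 0.922, so 7.8% narrower.

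**Split verdicts.** With the same true effect on both sides, each limb's test statistic is approximately normal with mean θ = 1.96 + z(power) and unit variance, and the two statistics have correlation r. Then P(exactly one significant) = 2 × [power − P(both significant)], with P(both) from the bivariate normal.

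- At 50% power, P(both) = 1/4 + arcsin(r)/(2π). For r = 0.7 this is 0.373, so the split probability is 2 × (0.5 − 0.373) = 0.253.
- At 80% power and r = 0.7, P(both) = 0.713, so the split probability is 2 × (0.8 − 0.713) = 0.174.

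| Assumed r | CI narrower with the mean | Split, 80% power per limb | Split, 50% power per limb |
|---|---|---|---|
| 0.95 | 1.3% | 7.1% | 10.1% |
| 0.9 | 2.5% | 10.0% | 14.4% |
| 0.8 | 5.1% | 14.2% | 20.5% |
| 0.7 | 7.8% | 17.4% | 25.3% |
| 0.5 | 13.4% | 22.6% | 33.3% |
| 0.3 | 19.4% | 26.8% | 40.3% |

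**Which rows apply.** The article names only group as independent variable for the comparison at T1. Raw forces then carry the large, stable differences between children, which both legs share, so a high r (0.7 to 0.95) is the plausible range. The rows for 0.5 and 0.3 become relevant only if T0 is also adjusted for, because that removes most of the shared part and leaves mainly per-reading error.

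**Effect on power.** If one limb has 80% power, θ = 2.80. The mean has power Φ(θ/√((1 + r)/2) − 1.96): 86.0% at r = 0.7 and 82.0% at r = 0.9.

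**With no true effect.** The chance that at least one of the two sides is significant is 7.0% at r = 0.9 and 9.1% at r = 0.5, against 5% for a single averaged outcome.

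**The case against.** Dynamometry is done limb by limb, and reporting each limb is transparent and loses no data, since the mean can be computed at any time. The article presents estimates with confidence intervals, so a reader of a split result would usually see two similar estimates with overlapping intervals. The wording about separate dependent variables covers every row of Table 2 and may not be a considered decision about limbs. The trial is sized on VO2peak/kg, not strength. Merging sides reduces the primary rows only from 14 (six aerobic, four strength, four fatigue) to 12, which leaves the wider question of many primary variables untouched. That the training is two-sided is inferred from the exercises and not stated.

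Most of this stands, and it limits the weight of the point. It does not remove it: the article states how the limb rows are analysed and judges each by its own interval, and no question in it requires separate sides. Descriptive reporting of each limb would keep the transparency.

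Two stronger readings are tempting.

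- A reader might infer that the two sides could show effects in opposite directions. The calculation concerns one side significant and the other not, with the same true effect.
- A reader might infer a large loss of power. A scenario can be built that shows 63% for one side against 86% for the mean: 15 per arm, T0-adjusted, 15% gain, between-child SD 30%, side SD 5%, common change SD 5%, reading error 12%. Its inputs imply a left-right correlation after adjustment of only about 0.14. The T0 slope is 925/1069 = 0.865, the residual variance is 1094 − 925²/1069 = 293.6, and the residual covariance is 925 − 2(0.865)(900) + (0.865²)(900) = 41.3, so r = 41.3/293.6 = 0.14. None of these inputs is in the document, and no T0 covariate is named. Without T0 adjustment the same scenario gives power of roughly 22% to 24% for one side and for the mean alike.

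**Conclusion.** The point holds as an optional improvement, not as an error that threatens the trial. Primary strength is analysed as four single-limb outcomes that the stated aims do not call for, and no summary per muscle group is named.

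The main consequence is interpretive: about a 10% to 25% chance per muscle group that only one side is significant when both truly respond alike (assumed r 0.7 to 0.9, power per limb 50% to 80%). The loss of precision is small for the T1 comparison as written, about 1% to 8% of interval width (assumed r 0.95 to 0.7). It would be 13% to 19% (assumed r 0.5 to 0.3) only under a T0-adjusted analysis. The direction is the same for any correlation below 1 when the sides have similar variance; the size rests on correlations that the document does not give.

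**What to change.** Define two primary strength outcomes: the mean of right and left maximal force for knee extensors, and the same for hip flexors. Equivalently, fit both sides of a muscle group in one model with a child random intercept and report one group effect per muscle group. If T0 and T1 enter the same model, add a child-by-visit term so that the two limbs at one visit are not treated as independent. Show right and left values descriptively.

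The cost is a changed entry in Table 2 and a sentence in the analysis text, ideally fixed before the data are analysed. No new measurement is needed. The only loss is a formal side-specific test, for which the article states no hypothesis.
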